### Trial-Specific Interventions

This is a pragmatic observational study with no imposed modifications to the standard surgical techniques employed at participating institutions. Each center will perform inguinoscrotal hernia repair on the basis of their routine clinical protocols and surgeon expertise.

Open group: may encompass anterior (Lichtenstein) or preperitoneal approaches, with mesh use and fixation technique determined by the operating surgeon.

Laparoscopic and robotic group: comprises TAPP or TEP techniques.

No restrictions regarding mesh type or fixation method are imposed; however, all intraoperative details (mesh type, fixation, use of drains, surgical time, and conversion) will be recorded for future analysis. Surgeons are anticipated to have completed their learning curve in the selected approach. Postoperative management, including analgesia, discharge criteria, and follow-up, will follow each center’s standard practice. This pragmatic approach ensures the study reflects real-world clinical scenarios and facilitates generalizability of the findings. To identify any variability between centers and detect potential confounders, all perioperative data will be systematically collected.

### Outcome Measures

Primary outcomes:The primary outcomes of this study encompass the postoperative outcomes.-Surgical site infection and surgical site occurrence will be analyzed, and general complication will be assessed and graded using the Clavien–Dindo classification system.Surgical site occurrence (SSO) was defined as any wound-related complication within 30 days after surgery, including both infectious and non-infectious events. SSO included seroma, hematoma, wound dehiscence, and SSI.Surgical site infections (SSI) were assessed within 30 days after surgery. SSI were classified as superficial, deep, or organ/space infections. Superficial SSI involved the skin and subcutaneous tissue, while deep SSI involved the fascia or muscle layers. Organ/space SSI referred to infections involving anatomical structures manipulated during surgery other than the incision.-Postoperative pain will be evaluated using the VAS.-The length of hospital stay will be recorded for all patients as a key marker of recovery.-Furthermore, the assessment of health-related QoL using the QoL questionnaires EuroQol EQ-5D-5LTM will continue.-Return to normal daily activitiesSecondary outcomes:The secondary endpoints will focus on long-term outcomes.-Evaluation of hernia recurrence-Chronic pain and health-related QoL will be assessed at long-term follow-up intervals.

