## Main and Secondary Hypothesis

We hypothesize that minimally invasive approaches—both laparoscopic and robotic—will lead to better early postoperative outcomes compared with open repair in patients with inguinoscrotal hernias. Specifically, we expect lower rates of surgical site infections and overall complications (as graded by the Clavien–Dindo classification), reduced postoperative pain as measured by the Visual Analogue Scale, and shorter hospital stays.

We also hypothesize that these advantages will translate into an improved early health-related quality of life, as assessed through the EQ-5D-5L questionnaire.

Regarding long-term results, we hypothesize that minimally invasive repair may be associated with lower rates of chronic pain and better long-term quality of life compared with open surgery.

Additionally, we expect that recurrence rates at 2 years will not significantly differ between minimally invasive and open approaches, reflecting comparable long-term durability of the repair.

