### Sample Size Calculation and Justification

The sample size was calculated to detect clinically significant differences in postoperative outcomes between minimally invasive (laparoscopic or robotic) and open approaches for inguinoscrotal hernias. Specifically, the calculation was based on the hypothesis that minimally invasive approaches would decrease postoperative complication rates by 20% compared with open surgery and lead to a 2-point reduction in postoperative pain (measured using the Visual Analog Scale).

Assuming a 5% significance level (two-sided α) and 80% power (1−β), and accounting for an estimated 5% loss to follow-up, a total of 150 patients (50 per surgical group: open, laparoscopic, robotic) will be required. This sample will enable the detection of statistically and clinically meaningful differences across the three groups using analysis of vairance (ANOVA) or Chi-square tests as appropriate.

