#### Postoperative Data

Surgical site eventsPostoperative adverse events (all occurrences other than surgical site occurrences, including ileus, pulmonary embolism, or pneumonia) according to the Clavien–Dindo Classification up to 30 daysDuration of analgesic medication useHospital readmission rateSick leave duration, defined as the number of days until return to work or to normal daily activitiesRecurrence rate, both clinically and radiologically (via ultrasonography or computed tomography), will be evaluated at 6 months, 1 year, and 2 years.QoL using the EuroQol EQ-5D-5LTM Spanish version: patients will receive questionnaires at inclusion and at 1, 6, 12, and 24 months postoperatively by mail, digitally, or in person according to their preference. Using the EQ-5DTM questionnaire, all participants will be asked to score the following five aspects of health status: mobility, self-care, usual activities, pain/complaints, and mood (anxiety/depression). This questionnaire is considered the most representative QoL tool for cost-effectiveness–related studies [14].Pain intensity using the VASReturn to normal daily activities

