#### Patient Timeline and Trial Visits

All patients scheduled for elective inguinoscrotal hernia repair (open, laparoscopic, or robotic approach) in the participating centers will be screened for eligibility and considered for study inclusion. Reasons for exclusion (whether owing to ineligibility or patient refusal) will be documented.

Patients who meet the inclusion criteria and can understand the scope of this study will be invited to participate. Written informed consent will be obtained after providing detailed information about the study objectives and procedures.

Baseline data collection will transpire during Visit 1, including demographic characteristics, comorbidities, clinical data, and the first QoL questionnaire. Visit 2 refers to the surgery day, where intraoperative and surgical details will be recorded. Postoperative outcomes and complications will be monitored during Visit 3 (discharge) and 4 (after 7 days). Moreover, any postoperative complication-related diagnostic or therapeutic interventions will be reported, and VAS scores will be calculated. To assess the persistence or recurrence of symptoms, long-term complications, reoperations, and QoL, follow-up will continue at Visit 5 (1 month), Visit 6 (6 months), Visit 7 (12 months), and Visit 8 (24 months) (Table 1).

**TABLE 1 T1:** Trial visits and documented parameters.

Assessment	Trial visits						
	Baseline	Day 0	Day 1	Day 7	Day 30	6 months	1 and 2 years
	Visit 1	Visit 2	Visit 3	Visit 4	Visit 5	Visit 6	Visit 7 and 8
Eligibility criteria	X	​	​	​	​	​	​
Informed consent	X	​	​	​	​	​	​
Demographic and baseline characteristics	X	​	​	​	​	​	​
Surgical details	​	X	​	​	​	​	​
Taken pain medication	​	​	X	​	X	​	​
Postoperative complication	​	​	X	​	X	​	​
Readmission rate	​	​	X	​	X	​	​
Sick leave	​	​	​	​	X	X	​
QoL assessment	X	​	X	​	X	X	X
VAS	X	​	X	X	X	X	X
Recurrence	​	​	​	​	​	X	X

Abbreviations: POD, postoperative day; QoL, quality of life; CCI, comprehensive complication index; V, visit; VAS, visual analog scale.

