### Statistical Analyses

Statistical analysis will follow the intention-to-treat principle. Descriptive statistics will be employed for summarizing baseline characteristics and perioperative outcomes across the three surgical groups: open, laparoscopic, and robotic.

Univariate analyses (Chi-square or Fisher’s exact test and ANOVA or Kruskal–Wallis test for categorical and continuous variables, respectively) will be performed for comparing outcomes, including complication rates, recurrence, surgical site infections, and hospital length of stay.

To control for potential confounders, multivariate logistic regression models will be applied, particularly for primary outcomes, including postoperative complications (classified using the Clavien–Dindo classification system and Comprehensive Complication Index), hernia recurrence, and chronic postoperative pain.

Time-to-event outcomes (e.g., time to recurrence) will be analyzed using Kaplan–Meier survival curves and compared using log-rank tests. To assess predictors of recurrence or reoperations, Cox proportional hazards models will be employed.

Subgroup analyses will be considered on the basis of patient age, BMI, hernia type (primary vs. recurrent), and surgical approach. P < 0.05 will be considered statistically significant.

To assess data quality, protocol adherence, and recruitment balance across centers, an interim descriptive analysis may be performed following the inclusion of 50% of the expected patient sample.

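### VAS pain is a primary outcome and a basis for the sample size, but no deciding early visit or summary is fixed; testing each early visit at 5% gives a false-positive rate of about 8–14%

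*Protocol article*

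**What the plan says.** - **Primary pain outcome.** Outcome Measures, under primary outcomes: "Postoperative pain will be evaluated using the VAS". No visit, change score or average is given. The same section fixes a 30-day window for surgical site infection and surgical site occurrence.
- **Sample size.** Sample Size Calculation and Justification assumes that minimally invasive repair will "lead to a 2-point reduction in postoperative pain (measured using the Visual Analog Scale"). It uses two-sided 5% alpha, 80% power, 5% loss and 50 patients per group (150 in total). It names neither a visit nor an SD for the VAS.
- **Schedule.** Table 1 ("Trial visits and documented parameters") ticks VAS at baseline, Visits 3, 4 and 5, 6 months, and 1 and 2 years. The text above it says "VAS scores will be calculated" in connection with Visits 3 and 4.
- **Early or late.** The main hypothesis is that minimally invasive repair "will lead to better early postoperative outcomes compared with open repair in patients with inguinoscrotal hernias", and it counts VAS pain among those early outcomes. Among the secondary outcomes: "Chronic pain and health-related QoL will be assessed at long-term follow-up intervals".
- **Tests.** Statistical Analyses names ANOVA or Kruskal–Wallis for continuous variables and logistic and Cox models for adjustment. It adds "P < 0.05 will be considered statistically significant", with no rule for repeated visits.
- **EQ-5D-5L.** It is listed as primary without a time point and again as long-term secondary. Postoperative Data says that "patients will receive questionnaires at inclusion and at 1, 6, 12, and 24 months postoperatively".

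**The concern.** This is multiplicity inside one endpoint, separate from the question of how many primary endpoints there are. Pain on Day 1, Day 7 and Day 30 need not point the same way, and nothing written settles which visit decides. The plan therefore leaves room to report the most favourable early visit as the primary pain result at an unadjusted 5%.

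The sample-size statement has the same gap. The SD of VAS may differ between visits, so a 2-point difference can mean different power at each. Without a named contrast, the 80% cannot be attached to any test.

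The named methods also leave a collected baseline VAS unused. Groups here are formed by centre practice and surgeon choice, so they may differ in pain before surgery. ANOVA and Kruskal–Wallis do not adjust for that, and the logistic and Cox models do not fit a continuous score.

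**Working it through.** **1. The plan's own figure.** For a difference of 2 points between two equal groups, n per group = 2 × (1.960 + 0.842)² × SD² / 2² ≈ 3.92 × SD², divided by 0.95 for loss. The article gives no SD, so 50 per group cannot be reproduced. Under assumed SDs:

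| Assumed SD | n per group | after 5% loss | power with 47 evaluable per group |
|---|---|---|---|
| 2 | 16 | 17 | 99.8% |
| 2.5 | 25 | 27 | 97.2% |
| 3 | 36 | 38 | 89.8% |
| 3.4 | 46 | 49 | 81.4% |
| 4 | 63 | 67 | 67.9% |

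(50 × 0.95 = 47.5, taken as 47.) Only an SD near 3.4 gives about 50. Power moves from about 68% to almost 100% as the SD goes from 4 to 2, so the statement has no definite meaning until the visit or summary and its SD are named.

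**2. False-positive rate over the three early visits.** Inputs: three early postoperative visits (Table 1) and a 5% threshold for each test (Statistical Analyses). The between-visit correlation ρ is an assumption and is varied.

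If independent: 1 − 0.95³ = 0.1426.

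If correlated, put Z_j = √ρ·U + √(1−ρ)·E_j for j = 1, 2, 3, with U and E_j standard normal, and find the probability that any |Z_j| exceeds 1.96. For the three-group ANOVA, use a 2-df chi-square at each visit and its 95% point. Both used 1,000,000 simulated draws with no true difference:

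| ρ | two groups, two-sided | three-group ANOVA |
|---|---|---|
| 0 | 14.3% | 14.3% |
| 0.3 | 13.6% | 13.6% |
| 0.5 | 12.5% | 12.7% |
| 0.7 | 10.9% | 11.1% |
| 0.8 | 9.9% | 10.0% |
| 0.9 | 8.4% | 8.5% |

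If correlation instead decays from one visit to the next (first-order autoregressive), the two-group rates are 12.9% at 0.5, 11.4% at 0.7 and 8.8% at 0.9. The structure matters little.

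**3. Direction.** Counting only false findings that favour minimally invasive repair (nominal 2.5%), the three early visits give 7.3% at ρ = 0, 6.3% at 0.5, 5.0% at 0.8 and 4.2% at 0.9.

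**4. After the fix.** One named estimate gives one test at 5%.

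**5. Timing statements side by side.**
- Visit 3 is discharge in the visit text and Day 1 in Table 1. Discharge criteria are left to each centre, so the two can fall on different days.
- Postoperative Data schedules one early EQ-5D-5L questionnaire after surgery, at 1 month. Table 1 also ticks Visit 3.
- Outcome Measures makes chronic pain secondary. Statistical Analyses names it among the primary outcomes for logistic regression.

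**The case against.** The strongest objection is that visit-by-visit testing is inferred. Statistical Analyses does not mention it, and VAS is not among the outcomes it names for univariate testing. Modelling of repeated measures is commonly left to a statistical analysis plan, which is not shown, and an article condenses. This stands in part: the model may come later, and the 8–14% is conditional on any early visit being allowed to decide. But the list of outcomes is open, the only methods offered for continuous variables are ANOVA and Kruskal–Wallis, and the time point of a primary outcome that drives the sample size belongs in the protocol. The authors did set a time frame for wound outcomes.

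Three stronger readings are tempting and are not supported.

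- A reader might infer that the error rate is at least double the stated 5%. For three early visits that holds only below a correlation of about 0.8, and the article gives no correlation.
- A reader might count all six postoperative visits, for 10.8% (ρ = 0.9) to 26.5% (ρ = 0). The hypotheses and Outcome Measures place late pain mainly under secondary outcomes, so this is not the primary error rate. The loose listing of chronic pain as primary in Statistical Analyses is a conflict to resolve, not a basis for that figure.
- A reader might extend the calculation to two early EQ-5D-5L assessments. The second exists only as the Visit 3 tick in Table 1, which Postoperative Data does not schedule.

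It is also fair to say that a significant three-group test need not favour minimally invasive repair. The directional rates in the working allow for that: lower, but still above their nominal 2.5%.

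**Conclusion.** The point holds for the early visits. The primary pain outcome has no deciding visit or summary, and its 2-point, 80% power statement belongs to no identifiable test. The size of the inflation rests on three assumptions: the named tests are applied at each of the three early visits, any one of them may be called the primary pain result, and the between-visit correlation lies between 0 and 0.9. EQ-5D-5L shares the missing early time point, but no error rate is claimed for it. The change should be made before the short-term outcomes are analysed.

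**What to change.** 1. **Name one primary pain estimate** in Outcome Measures and Statistical Analyses: minimally invasive minus open VAS, either at one named early visit or as the mean over the early visits from a repeated-measures model. Adjust it for baseline VAS and for listed baseline confounders.
2. **Tie the 2-point effect to it** in the sample-size section, with its assumed SD. If the mean over three visits is chosen, a single-visit SD does not carry over: with equal visit SDs and common correlation ρ, the SD of the mean is SD × √((1 + 2ρ)/3), for example 0.82 × SD at ρ = 0.5.
3. **Report as secondary** the other early visits and all 6-, 12- and 24-month VAS results.
4. **EQ-5D-5L:** name the 1-month score, adjusted for the score at inclusion, as the early primary estimate, and reconcile Postoperative Data with the Visit 3 tick in Table 1.
5. **Reconcile** Visit 3 as discharge with Visit 3 as Day 1, and the status of chronic pain between Outcome Measures and Statistical Analyses.

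Cost: changes of wording, using data already scheduled, plus a restated VAS power statement. A difference seen only at another visit can no longer be claimed as the primary result.

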### Data Collection and Analysis

#### Patient Baseline Characteristics

AgeSexBody mass index (BMI)ASA physical statusComorbidities (as assessed using the Charlson Comorbidity Index)—will be recorded.Type of hernia and classification

#### Intraoperative Data

Surgical approach (open, laparoscopic, or robotic)Surgical techniqueOperative timeMesh typeMesh sizeSpace of mesh placementConversionHospital stay

#### Postoperative Data

Surgical site eventsPostoperative adverse events (all occurrences other than surgical site occurrences, including ileus, pulmonary embolism, or pneumonia) according to the Clavien–Dindo Classification up to 30 daysDuration of analgesic medication useHospital readmission rateSick leave duration, defined as the number of days until return to work or to normal daily activitiesRecurrence rate, both clinically and radiologically (via ultrasonography or computed tomography), will be evaluated at 6 months, 1 year, and 2 years.QoL using the EuroQol EQ-5D-5LTM Spanish version: patients will receive questionnaires at inclusion and at 1, 6, 12, and 24 months postoperatively by mail, digitally, or in person according to their preference. Using the EQ-5DTM questionnaire, all participants will be asked to score the following five aspects of health status: mobility, self-care, usual activities, pain/complaints, and mood (anxiety/depression). This questionnaire is considered the most representative QoL tool for cost-effectiveness–related studies [14].Pain intensity using the VASReturn to normal daily activities

#### Patient Timeline and Trial Visits

All patients scheduled for elective inguinoscrotal hernia repair (open, laparoscopic, or robotic approach) in the participating centers will be screened for eligibility and considered for study inclusion. Reasons for exclusion (whether owing to ineligibility or patient refusal) will be documented.

Patients who meet the inclusion criteria and can understand the scope of this study will be invited to participate. Written informed consent will be obtained after providing detailed information about the study objectives and procedures.

Baseline data collection will transpire during Visit 1, including demographic characteristics, comorbidities, clinical data, and the first QoL questionnaire. Visit 2 refers to the surgery day, where intraoperative and surgical details will be recorded. Postoperative outcomes and complications will be monitored during Visit 3 (discharge) and 4 (after 7 days). Moreover, any postoperative complication-related diagnostic or therapeutic interventions will be reported, and VAS scores will be calculated. To assess the persistence or recurrence of symptoms, long-term complications, reoperations, and QoL, follow-up will continue at Visit 5 (1 month), Visit 6 (6 months), Visit 7 (12 months), and Visit 8 (24 months) (Table 1).

**TABLE 1 T1:** Trial visits and documented parameters.

Assessment	Trial visits						
	Baseline	Day 0	Day 1	Day 7	Day 30	6 months	1 and 2 years
	Visit 1	Visit 2	Visit 3	Visit 4	Visit 5	Visit 6	Visit 7 and 8
Eligibility criteria	X	​	​	​	​	​	​
Informed consent	X	​	​	​	​	​	​
Demographic and baseline characteristics	X	​	​	​	​	​	​
Surgical details	​	X	​	​	​	​	​
Taken pain medication	​	​	X	​	X	​	​
Postoperative complication	​	​	X	​	X	​	​
Readmission rate	​	​	X	​	X	​	​
Sick leave	​	​	​	​	X	X	​
QoL assessment	X	​	X	​	X	X	X
VAS	X	​	X	X	X	X	X
Recurrence	​	​	​	​	​	X	X

Abbreviations: POD, postoperative day; QoL, quality of life; CCI, comprehensive complication index; V, visit; VAS, visual analog scale.

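### Visit 3 is discharge in the text but Day 1 in Table 1, so the day of the earliest postoperative pain score, part of a primary outcome with no named time point, is not fixed

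*Protocol article*

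**What the plan says.** The narrative in Patient Timeline and Trial Visits states: "Postoperative outcomes and complications will be monitored during Visit 3 (discharge) and 4 (after 7 days". It then adds that "any postoperative complication-related diagnostic or therapeutic interventions will be reported, and VAS scores will be calculated", without naming a visit for the VAS.

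Table 1 ("Trial visits and documented parameters") puts Visit 3 under the heading Day 1 and Visit 4 under Day 7. It ticks VAS at baseline, Visit 3, Day 7, Day 30, 6 months, and 1 and 2 years.

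Outcome Measures lists pain among the primary outcomes with only this: "Postoperative pain will be evaluated using the VAS". The sample size section uses a 2-point VAS reduction as one of its two target effects. Neither section gives a day.

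Two further statements bear on the point. The hypotheses expect "reduced postoperative pain as measured by the Visual Analogue Scale, and shorter hospital stays" after minimally invasive repair. Trial-Specific Interventions says: "Postoperative management, including analgesia, discharge criteria, and follow-up, will follow each center’s standard practice".

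On quality of life, Postoperative Data says "patients will receive questionnaires at inclusion and at 1, 6, 12, and 24 months postoperatively by mail, digitally, or in person".

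**The concern.** A discharge visit and a Day 1 visit are different measurement times. Day 1 is the same for every patient. Discharge depends on the patient, the center and, by the study's own hypothesis, the surgical approach.

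If sites follow the text, the approach helps to decide when the first postoperative pain score is taken. Patients who leave sooner are scored sooner, when pain is usually higher. All patients are scored only once they are judged fit to go home, which narrows the contrast further. Both effects work against the group expected to leave earlier. Eight centers could also read the two labels differently, which would add a center effect to the timing.

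The conflict matters because no day is named for the primary pain outcome. The hypotheses place pain among the early results, and Visit 3 is the earliest postoperative VAS, so it is a natural candidate for the primary score.

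**Working it through.** **1. The text and table side by side**

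| Item | Text | Table 1 |
|---|---|---|
| Visit 3 | Discharge | Day 1 |
| Visit 4 | After 7 days | Day 7 |
| Complications at Visit 4 | Monitored | Not ticked |
| QoL at Visit 3 | Not listed (inclusion, 1, 6, 12, 24 months) | Ticked |
| VAS at Visit 3 | No visit named; the sentence follows the Visit 3 and 4 monitoring | Ticked |

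The table's day headings and visit numbers line up, so the Visit 3 conflict is not a fault of text extraction. Table 1 also ticks readmission at Visit 3, which cannot have happened yet if that visit is the discharge itself. The Day 7 and Day 30 VAS times agree in both places.

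**2. The plan's own sample size**

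The plan states 50 per group (150 in total), with two-sided α of 5%, 80% power and 5% loss. It gives no SD for VAS and no baseline complication rate, so 50 can be neither reproduced nor refuted. For VAS, n = 2(1.960 + 0.842)² × SD² / 2². An assumed SD of 3.45 gives 46.7, so 47, and 47 / 0.95 = 49.5, so 50. An SD of 2 gives 17 after inflation and an SD of 2.5 gives 27. The timing conflict changes none of these inputs, so the sample size is not in dispute here.

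**3. Size of a timing shift, if discharge governs**

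The document gives neither a pain slope nor a difference in stay. Both are assumptions.

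Shift = (fall in VAS per day) × (difference in day of discharge)

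| Fall per day | Difference in stay | Shift | Share of 2 points | A true 2-point benefit appears as |
|---|---|---|---|---|
| 0.5 | 0.5 day | 0.25 | 12.5% | 1.75 |
| 0.5 | 1 day | 0.5 | 25% | 1.5 |
| 1 | 0.5 day | 0.5 | 25% | 1.5 |
| 1 | 1 day | 1.0 | 50% | 1.0 |

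**4. What that would do to power, as illustration**

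Take two groups of 47 evaluable patients (50 × 0.95 = 47.5, rounded down). SE = SD × √(2/47), and power = Φ((2 − shift)/SE − 1.96). The SDs are assumed.

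| SD | SE | No shift | 0.25 | 0.5 | 1.0 |
|---|---|---|---|---|---|
| 2 | 0.413 | 99.8% | 98.9% | 95.3% | 67.9% |
| 2.5 | 0.516 | 97.2% | 92.4% | 82.9% | 49.2% |
| 3.45 | 0.712 | 80.2% | 69.1% | 55.9% | 29.0% |

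The loss is small for a small shift and a small SD, and large otherwise. With one fixed day for all groups, the difference in measurement day is 0 and so is the shift.

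**The case against.** The strongest reply is that the text never says VAS is taken at discharge. The only explicit VAS schedule is Table 1, and there the column is Day 1. On that reading no timing difference arises. Two later scores, at Day 7 and Day 30, are consistent in both places and could equally serve an early pain outcome. This stands to the extent that the bias is conditional and touches only the earliest postoperative score. It does not remove the contradiction: a site following the narrative would do Visit 3, VAS included, at discharge. Since no primary day is named, the later scores do not settle which score counts.

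A reader might also go further than the document allows:

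- **Return to daily activities is not collected.** Table 1 has no row under that name. But Postoperative Data defines sick leave as days until return to work or normal activities, and Table 1 has a sick-leave row at Day 30 and 6 months. At most this is a matter of labeling.
- **Complication ticks stop too early.** They end at Day 30, which matches the 30-day window for wound events and Clavien–Dindo events.
- **Late reoperations are captured unevenly.** The narrative says "To assess the persistence or recurrence of symptoms, long-term complications, reoperations, and QoL, follow-up will continue at Visit 5" and carries it on through Visits 6 to 8 for all patients. A row missing from a condensed article table does not show uneven capture.
- **The bias could reverse the planned effect.** Under the assumed ranges a true 2-point benefit still appears as 1.0 to 1.75 points. A reversal would need a true benefit smaller than the shift, which is not what the plan assumes.

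**Conclusion.** The contradiction on Visit 3 is real and should be corrected. If the discharge label governs, the first postoperative VAS is taken at a time that depends on surgical approach and center, and a true advantage of minimally invasive repair would tend to be understated. If Day 1 governs, there is no such problem. The direction rests on pain falling over the first days and on stay being shorter after minimally invasive repair, as the plan hypothesizes. The range of 0.25 to 1 point rests wholly on assumed values for slope and stay and is only an illustration. The QoL and Day 7 complication mismatches are minor: they need reconciling, but no primary event has been shown to be lost through them, since the Day 30 tick closes the complication window.

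**What to change.** In Patient Timeline and Trial Visits:

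1. Define Visit 3 as Day 1, as Table 1 already does, and collect its VAS on that postoperative day in all groups, remotely for patients who have gone home.
2. Keep the discharge date only for length of stay, which is already recorded.
3. In Outcome Measures, name one fixed postoperative day as the primary VAS time point.
4. Settle whether QoL is collected at Visit 3, and make Postoperative Data and Table 1 agree.
5. Settle whether complications are recorded at Visit 4, and make the text and Table 1 agree.

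The cost is edits to the text, Table 1 and the eCRF; no visit is added. The one practical burden is a remote VAS for early discharges. The change is best made before more data accrue, because differences in measurement day cannot be undone once scores have been collected.

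### Visit 3 is discharge in the text but Day 1 in Table 1, so the first postoperative VAS score can be timed by discharge, which the study expects to differ by approach

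*Protocol article*

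**What the plan says.** All references are to the protocol article.

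- **Patient Timeline and Trial Visits, text:** "Postoperative outcomes and complications will be monitored during Visit 3 (discharge) and 4 (after 7 days". The same paragraph adds that "VAS scores will be calculated".
- **Table 1 ("Trial visits and documented parameters"), same section:** the Visit 3 column is headed Day 1 and the Visit 4 column Day 7. VAS is ticked at Visits 1, 3, 4, 5, 6, 7 and 8. QoL is ticked at Visit 3 but not at Visit 4.
- **Outcome Measures:** among the primary outcomes, "Postoperative pain will be evaluated using the VAS". No time point is given. Length of hospital stay is also listed as a primary outcome.
- **Sample Size Calculation and Justification:** minimally invasive repair is assumed to "lead to a 2-point reduction in postoperative pain", again without a time point, and without an SD.
- **Main and Secondary Hypothesis:** the study expects "reduced postoperative pain as measured by the Visual Analogue Scale, and shorter hospital stays" after minimally invasive repair.
- **Trial-Specific Interventions:** "Postoperative management, including analgesia, discharge criteria, and follow-up, will follow each center’s standard practice".

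Nothing in the article says that every patient leaves on Day 1, or which definition of Visit 3 prevails.

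**The concern.** Postoperative pain changes quickly in the first days, so two groups can be compared on early pain only if they are measured at the same time since surgery. Table 1 gives that. The text does not: it ties Visit 3 to an event whose timing is itself a primary outcome and is hypothesised to depend on the approach.

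On the protocol's own hypothesis, a discharge-timed VAS would be read earlier after minimally invasive repair, when pain is probably higher, and later after open repair, when it is probably lower. That would shrink or hide a real benefit of minimally invasive repair, or make equal approaches look different. Because discharge criteria and choice of approach both follow center practice, differences between centers could also shift the comparison, in either direction.

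Adjusting for day of assessment afterwards would not cleanly repair this, since discharge day may be a consequence of the approach. A Day 1 score that was never taken cannot be recovered.

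**Working it through.** **1. The two definitions side by side**

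| Visit | Text | Table 1 | VAS in Table 1 | Agree? |
|---|---|---|---|---|
| 3 | Discharge | Day 1 | Yes | Only if the patient leaves on Day 1 |
| 4 | After 7 days | Day 7 | Yes | Yes |
| 5 | 1 month | Day 30 | Yes | Yes |
| 6 | 6 months | 6 months | Yes | Yes |
| 7, 8 | 12 and 24 months | 1 and 2 years | Yes | Yes |

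One of the six postoperative VAS occasions is in conflict. It is the first one.

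**2. The plan's own figure**

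The only stated number that rests on the VAS effect is 50 per group. With two-sided alpha 0.05, 80% power and a difference of 2 points, the evaluable n per group is 2 × (1.960 + 0.842)² × SD² / 2² = 3.92 × SD², rounded up and then divided by 0.95 for the 5% loss.

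- SD 2: 16, then 17 per group
- SD 2.5: 25, then 27
- SD 3: 36, then 38
- SD 3.45: 47, then 50

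Because no SD is stated, 50 cannot be reproduced from the document. The sample size also rests on complications, so it does not imply SD 3.45 for pain. The visit conflict changes no sample size.

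**3. Illustration of the timing artefact**

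The article gives no pain course, SD or discharge days. Everything in this step is assumed: VAS falls by 0.5 to 1.0 point per day, mean discharge is 0.5 to 1 day later after open repair, SD is 2 to 2.5, and there are 47 evaluable patients in each of two groups (50 less 5%, rounded down).

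Artefact = daily fall × difference in mean discharge day:

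- smallest: 0.5 × 0.5 = 0.25 point, 0.25 / 2 = 12.5% of the target
- middle: 0.5 × 1, or 1.0 × 0.5 = 0.5 point, 25% of the target
- largest: 1.0 × 1 = 1.0 point, 50% of the target

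SE = SD × √(2/47), which is 0.413 at SD 2 and 0.516 at SD 2.5. The chance of a significant result in the direction of the artefact when the approaches are truly equal at a fixed time is Φ(artefact/SE − 1.96). Power for a true 2-point benefit when open patients leave later is Φ((2 − artefact)/SE − 1.96).

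| Artefact | False difference, SD 2 / SD 2.5 | Power for a true 2 points, SD 2 / SD 2.5 |
|---|---|---|
| 0 (fixed Day 1) | 2.5% / 2.5% | 99.8% / 97% |
| 0.25 | 9% / 7% | 99% / 92% |
| 0.5 | 23% / 16% | 95% / 83% |
| 1.0 | 68% / 49% | 68% / 49% |

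The lower end of the range is nearly harmless for power and the upper end is not. The document does not allow a choice between them. These figures concern a comparison made at Visit 3 only.

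**The case against.** The strongest reply is that this is a labelling slip of limited reach. Five of the six postoperative VAS occasions are consistent, no section names Visit 3 as the time point for the primary pain comparison, and Table 1 already holds a fixed-time schedule. If the table governs, or if the comparison is made at Day 7 or Day 30, no bias arises. A single electronic case report form (Data Management) also makes it less likely that centers work to different definitions. All of this stands and limits the point to Visit 3. It does not remove it: the article does not say that the table prevails, and because no other VAS time point is fixed for the primary outcome, Visit 3 is not ruled out.

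Three stronger readings are tempting, and the document does not support them.

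- **That the pain comparison loses most of its power.** Suppose VAS = 5·exp(−k × day) with k from 0.15 to 0.35, all minimally invasive patients leave on day 1 and all open patients on day 2 or 3. The gap is then 0.60 to 1.04 or 1.12 to 1.77 points, and with SD 3.44 power for a true 2-point benefit falls to between 6% and 50%. This needs an assumed pain curve, complete separation of discharge days, and an SD back-solved as though pain alone set the sample size. If only half of the open patients leave on day 2 and the rest on day 1, the day-2 gap halves to 0.30 to 0.52 point.
- **That Visit 4 is equally ambiguous**, meaning 7 days after discharge. Table 1 fixes it at Day 7 with surgery as Day 0, and the other visits in that paragraph are counted from surgery, so this reading is strained.
- **That early EQ-5D scores are biased in the same way.** Postoperative Data schedules EQ-5D at inclusion and at 1, 6, 12 and 24 months. Whether a Visit 3 questionnaire exists at all is a separate inconsistency, to be settled first.

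**Conclusion.** The concern holds for the Visit 3 VAS. The text and Table 1 define that visit differently, the outcome is primary with no time point fixed elsewhere, and the text's definition ties measurement to an event that the study expects to differ by approach and leaves to local practice. It is an internal inconsistency; nothing shows that the authors chose discharge timing deliberately.

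The bias arises only if the text is followed, and only at the first postoperative assessment. Its size is unknown. The range of 0.25 to 1.0 VAS point is an illustration that rests on an assumed daily fall in pain and an assumed gap in mean discharge day, not an estimate for this study. If open patients do leave later, the likelier direction is against minimally invasive repair, so the study could miss the benefit it was set up to find.

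**What to change.** 1. Make the text agree with Table 1: take the Visit 3 VAS on postoperative Day 1 for every patient, with a short stated window, by phone or digitally if the patient is already home.
2. Record the discharge date as a separate item and use it for length of stay only.
3. State that no discharge-timed VAS enters the comparison between approaches, and name the time point of the primary VAS comparison.
4. Separately, settle whether EQ-5D is collected at Visit 3. It is ticked in Table 1 but absent from the schedule under Postoperative Data. There is no need to add a Day 7 EQ-5D, which neither place schedules.

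The cost is a wording change and a remote VAS contact for patients discharged before Day 1, with some risk of missed contacts in that group. No extra patients are needed and clinical care does not change. Data already collected at Visit 3 should carry the actual assessment date, so that off-schedule scores can be identified.
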